### EEG Signature of Emotion Recognition

To record the brain signature of emotions differentiation in voice, soundless methods may be more suitable since the recording process does not interfere with the acoustic stimulus that has to be processed. EEG, and particularly the analysis of Event-Related Potentials (ERPs), has been widely used to study the neuronal activation process of emotions. Furthermore, thanks to its high temporal resolution, ERPs analysis enable the distinction within attentional, sensory, and higher cognitive stages (Fan and Cheng, 2014). Early automatic auditory perception is usually observed between 100 and 250 ms over frontal and central cortices after stimulus onset (MMN). Higher amplitude of this component indicates higher discrimination of acoustic modulations relative to constant auditory background (Charpentier et al., 2018). As an index of acoustic changes early discrimination, the MMN can be used as an indicator of emotional prosody detection (Lindström et al., 2016, 2018; Paris et al., 2018). If automatic changes discrimination was salient enough, involuntary attentional switch to deviant auditory stimuli happens, and is observed 200–350 ms after stimulus onset at fronto-central cortices as a component known as P3a (Lindström et al., 2018; Paris et al., 2018). Early emotional recognition, valence, and arousal identification appear over frontal and central electrodes between 250 and 350 ms after the stimulus onset (Paulmann et al., 2013). The analysis of the amplitude of the P200 component has allowed to distinguish different prosodies such as disgust (high amplitude) and fear (lower amplitude) (Paulmann et al., 2013). This component has shown to reflect the early arousal decoding and may predict the deeper processing of the emotional information observed in the 250–1,000 ms time-window after the stimulus onset (Paulmann, 2016; Steber et al., 2020). The time window between 400 and 1,000 ms has been related to the motivational relevance and extensive processing of the prosodic emotional stimulus. In such window, the observation of the Late Positive Potential (LPP) over centro-parietal recording sites is frequent (Steber et al., 2020). The LPP amplitude is higher in emotional than neutral stimuli, while it is shorter during the emotional down-regulation (Pan et al., 2020).

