#### Data Analysis

For ERP amplitude analysis, electrodes will be grouped according to regions of interest (ROIs). Left prefrontal site: FP1. Left frontal channels: F3, F7. Right prefrontal site: FP2. Midline pre-frontal site: AFz. Midline frontal electrode: Fz. Right frontal channels: F4, F8. Left temporal site: T7. Left central electrode: C3. Midline central electrode: Cz. Right temporal site: T8, Right central electrode: C4. Centro-parietal electrode: CPz. Left parietal sites: P3, P7. Midline-parietal electrode: Pz. Right parietal sites: P4, P8. Midline parieto-occipital electrode: POz. Left occipital site: O1. Right occipital site: O2. Maximum peak time window analysis will be: 100–250 ms for the MMN (Kujala et al., 2007; Paris et al., 2018), 170–230 ms for P200 component (Paulmann et al., 2013), 200 and 350 ms for the P3a (Kujala et al., 2007; Paris et al., 2018), and 400–1,000 ms for the LPP component (Steber et al., 2020).

Event-Related Potentials will be extracted by averaging the data obtained for standard and deviant stimuli, and for each condition independently. The ERPs elicited by standard stimuli will be subtracted from the ERPs elicited by deviants to calculate difference waves. The mean ERPs amplitude will be calculated as follows. For standard stimuli, level of naturalness and group average peak latencies will be determined from all ROIs. Mean amplitudes will be determined by considering a ±50-ms time window centered at the grand mean peak latency. For deviant stimuli, mean amplitudes will be calculated from the difference waves at ROIs. Mean amplitudes will be determined by considering a ±50-ms time window centered to the grand mean peak latency (Kujala et al., 2007; Paris et al., 2018).

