##### Statistical analysis

The statistical significance of ERP components will be tested by comparing their mean amplitudes to zero at ROIs using one-sample t-tests. This method will allow us to focus exclusively on significant responses, and to distinguish significant scalp distributions from noise. Statistically significant ERPs will be considered for further amplitude analysis.

For standard stimuli, levels of naturalness comparisons will be performed by Level × ROI repeated measures ANOVAs on each ERP and group independently. For deviant stimuli, Level × ROI × Deviant repeated measures ANOVAs will be performed.

Group comparisons will be conducted by Group × ROI repeated measures ANOVAs on each ERP and level of naturalness separately, for standard stimuli. Similarly, for deviant stimuli, Group × ROI × Deviant repeated measures ANOVAs will be performed. The effect of reducing the naturalness of voice on emotion processing will be assessed by the comparison between ERPs amplitudes at levels 1–5 for ASD group and ERPs amplitudes calculated in the control group for human voices. We expect to detect less natural voices to help typical processing in ASD children, that is, fewer difference with non-pathological processing of human voices at least natural voices. Based on MMN analysis at maximum peak ROI, the voice leading to the nearest to non-pathological processing in autistic children will be chosen for Stage 3.

Scalp distribution comparisons for standard stimuli will be assessed by Group × Laterality (FP1, F3, F7, T7, C3, P3, P7, O1/AFz, Fz, CPz, Cz, POz, Pz/FP2, F4, F8, T8, C4, P4, P8, O2) repeated measures ANOVAs on each ERP and level of naturalness separately. For deviant stimuli, Group × Laterality × Deviant repeated measures ANOVAs will be conducted.

For all amplitude analysis, normality will be assessed by Shapiro–Wilk test. In case of non-parametric distribution of the data, a transformation will be applied. Mauchly’s test of sphericity will be used to evaluate homogeneity of variances and co-variances. In case of violation of sphericity, a Greenhouse-Geisser correction will be applied in order to test main effects significance. *Post hoc* comparisons will be conducted to assess specific differences (Tukey and Dunnett procedures). In all cases, level of significance will be set at *p* < 0.05 and statistical analysis will be performed with R software.

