##### ERPs

For ERP amplitude analysis, electrodes will be grouped according to ROIs described in section “Data Analysis.” Maximum peak time windows used for data analysis of ERPs will be identical to the one mentioned in section “Data Analysis.” MMN, P200, P3a, LPP will be under study.

Event-Related Potentials will be extracted by averaging the data obtained for standard and deviant stimuli, and for each condition independently. The ERPs elicited by standard stimuli will be subtracted from the ERPs elicited by deviants to calculate difference waves. The mean ERP amplitude will be calculated as follows. For standard stimuli, group and assessment session average peak latencies will be determined from all ROIs for TD and ASD separately. Mean amplitudes will be determined by considering a ±50-ms time window centered to the grand mean peak latency. For deviant stimuli, mean amplitudes will be calculated from the difference waves at ROIs. Mean amplitudes will be determined by considering a ±50-ms time window centered to the grand mean peak latency (Kujala et al., 2007; Paris et al., 2018).

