##### Statistical analysis on ERPs data

The statistical significance of ERP components will be tested by comparing their mean amplitudes to zero at ROIs using one-sample *t*-tests. This method will allow us to focus exclusively on significant responses, and to distinguish significant scalp distributions from noise. Statistically significant ERPs will be considered for further amplitude analysis.

Group comparisons will be conducted by Group × ROI repeated measures ANOVAs on each ERP and assessment session separately, for standard stimuli. Similarly, for deviant stimuli, Group × ROI × Deviant repeated measures ANOVAs will be performed.

For standard stimuli, time comparisons will be conducted by Assessment Session × ROI repeated measures ANOVAs on each ERP and group separately. For deviant stimuli, Assessment Session × ROI × Deviant repeated measures ANOVAs will be performed.

Scalp distribution comparisons for standard stimuli will be assessed by Group × Laterality (FP1, F3, F7, T7, C3, P3, P7, O1/AFz, Fz, CPz, Cz, POz, Pz/FP2, F4, F8, T8, C4, P4, P8, O2) repeated measures ANOVAs on each ERP and assessment session separately. For deviant stimuli, Group × Laterality × Deviant repeated measures ANOVAs will be conducted.

For all amplitude analysis, normality will be assessed by Shapiro–Wilk test. In case of non-parametric distribution of the data, a transformation will be applied. Mauchly’s test of sphericity will be used to evaluate homogeneity of variances and co-variances. In case of violation of sphericity, a Greenhouse-Geisser correction will be applied in order to test main effects significance. *Post hoc* comparisons will be conducted to assess specific differences (Tukey procedure).

All statistical analysis will be performed with R software. Level of significance will be set at *p* < 0.05.

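### MMN and P3a are tested on standard stimuli alone, where no deviance response exists, and on the difference wave the P200 search sits inside the MMN search with no polarity rule

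*Protocol article*

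**What the plan says.** **What the components mean.** The introduction (EEG Signature of Emotion Recognition) says of the MMN: "Higher amplitude of this component indicates higher discrimination of acoustic modulations relative to constant auditory background". The same section describes P3a as an involuntary switch of attention to deviant sounds.

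**How amplitudes are obtained (Stage 2, Data Analysis).** Each component has one search window for its maximum peak: MMN 100–250 ms, "170–230 ms for P200 component", P3a 200–350 ms, LPP 400–1,000 ms. Standards have their own rule, a mean over ±50 ms around the grand mean peak latency. For deviants, "The ERPs elicited by standard stimuli will be subtracted from the ERPs elicited by deviants to calculate difference waves", and "For deviant stimuli, mean amplitudes will be calculated from the difference waves at ROIs", again over ±50 ms. No component is assigned to one waveform or the other, and no polarity is stated for any peak search.

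**What is tested (Stage 2, Statistical analysis).** For standards, "levels of naturalness comparisons will be performed by Level × ROI repeated measures ANOVAs on each ERP and group independently". Group comparisons use "Group × ROI repeated measures ANOVAs on each ERP and level of naturalness separately, for standard stimuli". Group × Laterality ANOVAs on standards are also run for each ERP and level. Components enter only if a one-sample t-test finds their amplitude different from zero. The Stage 3 voice is chosen on the MMN analysis at the maximum-peak ROI; the waveform is not named.

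**Stage 3.** The ERPs section says "MMN, P200, P3a, LPP will be under study" and repeats the amplitude rules. Statistical analysis on ERPs data plans "Group × ROI repeated measures ANOVAs on each ERP and assessment session separately, for standard stimuli", with matching session and laterality ANOVAs.

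**The concern.** There are two linked problems.

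First, the standards are the constant background against which MMN and P3a are defined. The averaged response to standards contains no deviance contrast. What is found there at 100–250 ms or 200–350 ms is the evoked response to a neutral word. If groups, naturalness levels or sessions differ on it, the plan's labels would turn this into altered discrimination or altered attention switching.

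Second, on the difference wave the plan looks for P200 within a stretch of time that also belongs to MMN, without saying that one peak is negative and the other positive. The introduction gives them different meanings: early acoustic discrimination for MMN, early arousal decoding for P200. One change in MMN could therefore surface as two findings at two cognitive stages.

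The MMN also decides which voice goes into the intervention. Since the text computes an amplitude for standards as well as for deviants, the waveform behind that decision should not be left open.

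**Working it through.** The plan gives no figure to reproduce here. The check is a count of the tests, interval arithmetic on the stated windows, and one illustration.

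**1. ANOVAs on standards implied by a literal reading.** Inputs: 4 components; Stage 2 has 2 groups and 6 voices (5 levels plus human); Stage 3 has 4 groups and 5 assessments (pre, mid, end, and 2 and 6 weeks after). The count assumes that every component passes the t-test against zero.

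| Stage | Analysis | Count |
|---|---|---|
| 2 | Level × ROI, per ERP and group | 4 × 2 = 8 |
| 2 | Group × ROI, per ERP and level | 4 × 6 = 24 |
| 2 | Group × Laterality, per ERP and level | 4 × 6 = 24 |
| 2 | **Total** | **56** |
| 3 | Group × ROI, per ERP and session | 4 × 5 = 20 |
| 3 | Session × ROI, per ERP and group | 4 × 4 = 16 |
| 3 | Group × Laterality, per ERP and session | 4 × 5 = 20 |
| 3 | **Total** | **56** |

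MMN and P3a are 2 of the 4 components, so 56 × 2/4 = 28 in each stage carry a label that does not fit the waveform. The t-test does not prevent this: a sound-evoked response to standards differs from zero without any deviance being present.

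**2. Search windows.** Overlap = min(ends) − max(starts).

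- MMN and P200: 230 − 170 = 60 ms, which is all of the P200 window and 60/150 = 40% of the MMN window.
- MMN and P3a: 250 − 200 = 50 ms, 33% of each.
- P200 and P3a: 230 − 200 = 30 ms, 50% of the P200 window.
- LPP shares no search window with the others.

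**3. Averaging windows.** Each is 100 ms wide, so two of them share max(0, 100 − |difference in peak latency|) ms.

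- MMN at 175 ms, P200 at 200 ms: 100 − 25 = 75 ms.
- MMN at 150 ms, P200 at 200 ms: 50 ms.
- Equal latencies: 100 ms, the same measure.
- MMN at 130 ms or earlier, P200 at 230 ms: 0 ms.

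Over all admissible latency pairs on the 2 ms sampling grid, weighted equally (an assumption), the mean overlap is about 56 ms; 94% of pairs overlap at all and 62% by at least 50 ms.

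**4. Illustration of leakage.** Assumed difference wave, not from the protocol: a Gaussian MMN of −3 µV (SD 35 ms) and a Gaussian P3a of +2.5 µV at 280 ms (SD 40 ms), with no P200 effect. Only the MMN is halved.

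| MMN peak | Change in MMN measure | Change in P200 measure at 200 ± 50 ms | Change in P200 measure at 230 ± 50 ms |
|---|---|---|---|
| 175 ms | 1.11 µV | 0.98 µV (−1.38 to −0.40) | 0.58 µV |
| 150 ms | 1.10 µV | 0.66 µV | 0.26 µV |
| 130 ms | 1.10 µV | 0.38 µV | 0.10 µV |

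The 230 ms column is where a search for the largest positive value within 170–230 ms would land on this wave. With the MMN at 175 ms, a search for the largest absolute value picks 174 ms for both components, and the two measures coincide. The missing polarity rule thus decides whether P200 is partly or entirely the MMN.

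**The case against.** The best defence is that no sentence says outright that all four components are scored on standards. The protocol also uses the term ERPs for whole waveforms, and limits further analysis to significant ones, so the phrase about each ERP could mean whichever responses the standards elicit. A condensed article may also leave the assignment of components to waveforms to a fuller plan. This softens the point but does not remove it. The article itself sets out the windows, the two amplitude rules and the ANOVAs, names four components, and excludes none for standards.

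A second defence concerns P200 on the difference wave. Deviants are emotional and standards neutral, so the subtraction is already an emotional-minus-neutral contrast and a legitimate one. That stands. The defect is the nested search without polarity and the reading of the result as a separate stage.

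A reader might go further and infer that P200 and MMN are practically the same number. The documents do not support this. Only the search windows are nested; the averaging windows may be identical, partly shared or disjoint, and the leakage of about 1 µV arises only for particular assumed latencies.

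A reader might also fault the LPP measure because it averages 100 ms out of a 600 ms window and could run past the epoch. A mean around a peak is a stated, computable measure. The epoch ends at 1,100 − 100 = 1,000 ms, so an overrun needs a peak after 950 ms, which nothing in the protocol predicts.

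Finally, the voice choice concerns emotional processing, so the difference-wave MMN is its natural basis. That is probably the intention, but it should be written down.

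**Conclusion.** The point holds in a limited form. As written, MMN and P3a are tested on standards, which conflicts with the protocol's own description of both as responses to deviance. That affects 28 of 56 ANOVAs on standards in each stage, assuming that each ERP means each of the four named components and that all pass the t-test against zero.

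On the difference wave, P200 and MMN are not cleanly separated. Their averaging windows share between 0 and 100 ms, and the leakage of an MMN change into P200 depends on the peak latencies and on the unstated polarity rule. In the illustration, with a true P200 effect of zero, it runs from 0.10 to 0.98 µV for an MMN change of 1.1 µV; these values rest on the assumed wave shapes and show possibility, not an expected size.

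It does not follow that the ERP results are uninterpretable as a whole. P200 and LPP on standards are legitimate, the difference-wave MMN and P3a are sound, and the P200 measures do not enter the voice choice.

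**What to change.** In Data Analysis and Statistical analysis (Stage 2), and in ERPs and Statistical analysis on ERPs data (Stage 3):

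1. Score MMN as a negative peak and P3a as a positive peak, both on the deviant-minus-standard difference wave only.
2. Delete the ANOVAs on standards for MMN and P3a. This leaves 28 of 56 in each stage, for P200 and LPP.
3. State that the Stage 3 voice choice uses the difference-wave MMN.
4. For P200, do one of two things: score it as a positive peak on the unsubtracted ERPs, or keep it on the difference wave and state that an effect there will not be interpreted as a processing stage distinct from MMN.

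Averaging LPP over its full window, or recasting the analysis with a six-level emotion factor, is optional and not needed to correct this error.

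The cost is analysis wording. The recordings stay the same and there are fewer tests. If P200 moves to unsubtracted ERPs, the Stage 2 neutral average rests on 480 trials per block and each emotional average on 24, before artefact rejection, so peaks will be less precise for the emotional stimuli.

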#### Creation of Five Levels of Naturalness for Emotional Speech

Once acoustic features tendencies across naturalness levels will be defined, audio files from emotional human voices recordings will be edited in order to reduce naturalness in those speech signals. Spectral content will be filtered, intensity level and total duration (speech rate) will be adjusted. Acoustic signals edition will be realized using Matlab. For instance, if less naturalness is characterized by higher levels of harmonics-to-noise ratio [human speech is a noisy and continuous signal (Zatorre and Baum, 2012)], then frequencies that are not harmonics will be filtered. The edition of the signal will be applied on previously recorded in Stage 1 audio files for adult male, female, and children voices. Anger, fear, sadness, disgust, happiness, and neutral acoustic signals will be similarly adjusted. Naturalness will be progressively reduced to generate five different levels: from level 1: the less natural to level 5: the more natural voice. Level 1 will correspond to a 95% removal of naturalness, levels 2–5 will correspond to a 76, 57, 38, and 19% diminution, respectively. In accordance with this example, if less naturalness is characterized by higher levels of harmonics-to-noise ratio, then 95% of frequencies that are not harmonics will randomly be filtered for level 1, 76, 57, 38, and 19% of non-harmonics frequencies will be filtered for levels 2–5, respectively. All features defined as being part of naturalness characterization will be edited simultaneously.

Statistical analyses will be used to ensure that levels 1–5 and human voice differ as regard the acoustic parameters edited. Values obtained for each voice and emotion (e.g., adult male/anger, adult female/happiness, etc.) will be analyzed separately with one-way ANOVAs. Normality and homogeneity will be assessed using Shapiro–Wilk and Bartlett tests, respectively. In case of non-parametric distribution of the data, Kruskal–Wallis test will be applied. *Post hoc* comparisons will be conducted to assess specific differences (Tukey after ANOVA, Wilcoxon tests with *p*-value adjustment by Holm method after Kruskal–Wallis). In case of no statistical difference between levels, percentages of diminution of naturalness will be adjusted. Levels must differ for all parameters implicated in naturalness characterization.

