#### Passive Oddball Paradigm

Emotional and neutral words uttered by human voices recorded in stage 1 and synthesized voices created in stage 2 will be displayed to the participant. During the EEG recording, participants will sit on an armchair while watching a silent movie and will be instructed to pay no attention to the auditive stimuli. To facilitate the comparison of naturalness levels, six stimulus blocks will be created, each containing 600 stimuli corresponding to one of the five levels, or the human voice. Each block will consist of 480 frequently presented neutral-uttered standard stimuli (80%), and occasional 24 anger (4%), 24 disgust (4%), 24 fear (4%), 24 happiness (4%), and 24 sadness (4%) deviant stimuli. Standard and deviant stimuli will be equally uttered with a male, woman, or child voice. The stimuli will be presented pseudo-randomly with deviant stimuli being preceded by at least two standard stimuli. Each participant will listen to three blocks for an approximatively 30-min task. The stimulus sequences for each block will be fixed, and the order of blocks will be counterbalanced and randomized between participants. The stimulus onset asynchrony will be of 1,300 ms. The stimuli will be presented at 60 dB via the Shure SRH1840 audio headset that has a flat response frequency response in order to accurately reproduce the input audio signal. Autistic participants will be accompanied by their parent if necessary.

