#### Participants

Typically developed participants will be recruited from a public announcement posted on Tecnologico de Monterrey, Campus Monterrey. Autistic participants will be recruited by contacting parents of autistic children attending San Jose Hospital from Tecnologico de Monterrey.

Sample size estimation was calculated with G^∗^Power software version 3.1.9.7 (Faul et al., 2007) for Cohen’s d effect size index of 0.8, correlations among repeated measures of 0.5, statistical significance set at *p* < 0.05. For level comparisons, results indicated that 20 participants in each group would be enough to provide an estimated power of 0.90. For group comparisons, results indicated that 38 participants in each group would be enough to provide an estimated power of 0.91.

Forty high-functioning autistic volunteers aged 9 to 11-year-old will be involved in this stage of the research. All autistic participants will be diagnosed by a clinician according to DSM-V (Diagnostic and Statistical Manual of Mental Disorders, Fifth Edition) (American Psychiatric Association, 2013) or the International Classification of Diseases and Related Health Problems – Tenth Edition (World Health Organization, 1994) criteria. Autistic symptomatology will be assessed by the Autism Spectrum Rating Scales (ASRS) – parent report (Goldstein, 2012). A T-score greater than 60 (slightly elevated to very elevated scores for autistic behaviors) on Social/Communication, DSM-IV-TR (Text Revision), Peer and Adult Socialization and Social/Emotional Reciprocity domains will be considered as an inclusion criterion.

In addition, 40 TD volunteers aged 9 to 11-year-old will be included in this study. Similar to autistic children, ASRS will be used, and children with a score inferior to 60 in all scales will be included.

Any TD or autistic participant will be excluded if child:

•is under medication affecting the central or peripherical nervous system,•has hearing loss or deficits, and/or•has history of a developmental pathology and/or any disease affecting behavior and nervous system, apart from ASD for autistic participants.

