This project of investigation might encounter some pitfalls and unexpected results. Non-professionalism of actors recruited for emotional recordings during Stage 1 may affect the reliability of required prosodies. Nevertheless, the number of volunteers will be increased in order to generate four times more utterances than necessary to enable the selection of best actor participants. Furthermore, emotion recognition accuracy will be validated by supervised learning algorithm to ensure the quality of emotion discrimination based on acoustic features. Stage 2 aims to explore emotional recognition impairments in autism triggered by naturalness of human voices. We expect to observe a diminution of the amplitude of ERPs in the autistic population as a reflect of decreased attentional, sensorial, and cognitive emotional processing (Lartseva et al., 2015; Lindström et al., 2016, 2018). The autistic condition may also be characterized by hemispheric lateralization anomalies due to lateralized compensatory brain activity (Subbaraju et al., 2018). Impairments are expected to fade with the decreasing naturalness of voice stimuli. However, in the opposite case, no effect of naturalness on neural emotional processing by autistic children would be an evidence that the modulated acoustic parameters would not participate to autistic impairments. In the latter situation, or in case of enhancement of autistic impairments triggered by naturalness modulations, the acoustic edition of the stimuli will be reconsidered. Finally, Stage 3 expects the implementation of less natural voices in a robot-based intervention with the aim of improving emotion detection by autistic children. The 2-week intervention may imply a high rate of withdrawals whereas the sample size needed is relatively high. However, upon completion, we expect the intervention to trigger a reduction of autistic impairments (reduction of symptomatology, higher EEG activity, higher behavioral accuracy for emotion discrimination: smaller reaction times, and higher correct answers at end- and follow-up assessments).

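### Stage 2 expects a graded effect along an equally spaced naturalness scale but tests Level only as an unordered factor; a planned linear contrast beside the omnibus test would be a cheap improvement

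*Protocol article*

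**What the plan says.** All references are to Stage 2 of the protocol article unless stated.

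- **The scale.** Creation of Five Levels of Naturalness for Emotional Speech: "Level 1 will correspond to a 95% removal of naturalness, levels 2–5 will correspond to a 76, 57, 38, and 19% diminution, respectively". With the human voice at 0%, that is six points in equal 19-point steps. The same section allows the percentages to be adjusted if levels do not differ acoustically.
- **The hypothesis.** Discussion: "Impairments are expected to fade with the decreasing naturalness of voice stimuli". The Statistical analysis section likewise expects the autistic group to come closest to typical processing at the least natural voices.
- **The analysis.** Statistical analysis, for standard stimuli: "levels of naturalness comparisons will be performed by Level × ROI repeated measures ANOVAs on each ERP and group independently". The next sentence adds Deviant as a factor for deviant stimuli. Post hoc tests are Tukey and Dunnett. A separate comparison sets the autistic group at levels 1 to 5 against controls hearing the human voice, and the Stage 3 voice is then picked on the MMN.
- **The sizing.** Participants: an "effect size index of 0.8, correlations among repeated measures of 0.5". Then: "For level comparisons, results indicated that 20 participants in each group would be enough to provide an estimated power of 0.90". Enrolment is higher: "Forty high-functioning autistic volunteers aged 9 to 11-year-old will be involved in this stage of the research".
- **The exposure.** Passive Oddball Paradigm: "six stimulus blocks will be created, each containing 600 stimuli corresponding to one of the five levels, or the human voice". Each child hears three of these six.

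**The concern.** The hypothesis is about order, but the planned test of Level ignores order. An omnibus F test gives the same p-value if the level means are shuffled, so it cannot by itself show that the response moves steadily with naturalness. It also spreads a linear effect over 4 or 5 degrees of freedom where 1 would do. The comparison of the autistic group with controls on the human voice specifies no ordered test either, so the gap covers standards and deviants alike.

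The Discussion attaches a consequence to a null result: if naturalness shows no effect, the acoustic editing is to be reconsidered. Missing a real gradient could therefore send the project back to re-synthesis. Conversely, a significant omnibus result leaves the graded claim to be argued from pairwise comparisons or from a trend test chosen after the means are seen.

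**Working it through.** **Inputs.** Alpha 0.05, d = 0.8, correlation rho = 0.5, and 20 children per group for level comparisons with stated power 0.90 (Participants; Statistical analysis). Five synthesized levels, or six with the human voice. Forty autistic children, three of six blocks each (Passive Oddball Paradigm). Power is from the noncentral F distribution. SS is the sum of squared deviations of the level means, in standard deviation units.

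**Step 1. Reproduce the stated 0.90.** The article does not say which G*Power procedure was used. Two readings fit.

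- *One-way, 5 levels, 20 per level, f = d/2 = 0.40.* λ = 100 × 0.40² = 16; df 4, 95; power 0.896.
- *Within-subject, N = 20, equally spaced means with end-to-end difference 0.8.* λ = N × SS/(1 − rho). Five levels: SS = 0.400, λ = 20 × 0.400/0.5 = 16.0, power 0.892. Six levels: SS = 0.448, λ = 17.92, power 0.909.

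Within-subject with f = 0.40 gives 0.997 (five levels) or 0.999 (six), which does not fit.

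**Step 2. Trend test, same λ on 1 df, exactly linear truth.** In the within-subject rows, the lower trend figure uses the contrast's own error term (19 df) and the upper figure the pooled error.

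| Reading | Omnibus | Trend | Gain (points) |
|---|---|---|---|
| One-way, 5 × 20, f = 0.40 | 0.896 | 0.977 | 8.1 |
| Within, N = 20, 5 levels, range 0.8 | 0.892 | 0.966–0.977 | 7.5–8.5 |
| Within, N = 20, 6 levels, range 0.8 | 0.909 | 0.980–0.987 | 7.1–7.9 |

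At an omnibus power of 0.90 the gain cannot exceed 10 points, because power cannot exceed 1.

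**Step 3. The design as described.** Three of six blocks for 40 children gives 40 × 3/6 = 20 children per level if balanced. Taking this as balanced incomplete blocks (an assumption), the efficiency is (6 × 2)/(3 × 5) = 0.8 and the error df are 120 − 40 − 5 = 75.

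- Range 0.8: λ = 20 × 0.8 × 0.448/0.5 = 14.34; omnibus 0.817, trend 0.962, gain 14.5 points.
- f = 0.40: λ = 20 × 0.8 × (6 × 0.16)/0.5 = 30.72; omnibus 0.994, trend 1.000, gain 0.6 points.
- If all 40 heard every level (range 0.8), the omnibus would be 0.998 to 0.999 and the gain under 0.3 points.

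**Step 4. When the truth is not linear (six levels, range 0.8, rho 0.5).**

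| True pattern | Design | Omnibus | Trend |
|---|---|---|---|
| Level 1 only differs | Complete, N = 20 | 0.954 | 0.82–0.85 |
| Level 1 only differs | 3 of 6 blocks, N = 40 | 0.887 | 0.761 |
| Inverted U | Complete, N = 20 | 0.997 | 0.05 |

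**The case against.** The strongest case against has four parts.

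1. **Target.** The quoted sentence concerns neutral standard stimuli within each group. For the effect of reducing naturalness the plan names another comparison, autistic children at levels 1 to 5 against controls on the human voice. Level-versus-reference comparisons suit Dunnett, and a slope selects no voice. This stands in part: the trend cannot choose the Stage 3 voice. But the control reference is fixed, so a slope across levels in the autistic group does bear on whether impairment fades. The deviant analysis uses the same unordered factor.

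2. **Size.** A reader might infer a loss of 22 to 25 points. Reading 0.8 as the end-to-end difference in the one-way formula gives 0.580 against 0.799 for five levels (λ = 20 × 0.400 = 8.0) and 0.597 against 0.843 for six (λ = 20 × 0.448 = 8.96). The documents do not support this. It needs an omnibus power near 0.6 where the plan states 0.90, and it ignores the stated correlation of 0.5.

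3. **Shape.** The Discussion asks up to what degree removal helps and how processing varies with human-likeness, so thresholds and non-monotone patterns are open. The percentages may also change. This stands, and it is why the trend should not replace the omnibus test.

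4. **Preference.** Omnibus ANOVA with Tukey and Dunnett is valid, and Tukey already covers the extreme pair. Contrasts are often left to an analysis plan. The first part stands. On the second, the article itself fixes the model, sphericity correction and post hoc procedures for Level, so the mismatch with its own hypothesis can be raised here.

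**Conclusion.** The point holds as an efficiency gap: an ordered hypothesis on an equally spaced scale has no planned test that uses the order. For a linear effect the cost is about 7 to 9 points of power at the plan's own 0.90. It is about 15 points under a balanced three-of-six-block design with rho 0.5 and range 0.8, and close to none where omnibus power is already near 1. These figures assume an exactly linear truth and equal spacing; no dropout is applied, since Stage 2 states no allowance.

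A reader might go further and conclude that the planned ANOVA is wrong or should give way to the trend as the main test. The documents do not support that. The test is valid, and it is the better one for an effect at a single extreme level or a non-monotone pattern, which the Discussion leaves open. This is a cheap improvement, not a correction of an error.

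**What to change.** In the Stage 2 Statistical analysis section:

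- Pre-specify a linear contrast of ERP amplitude on percentage of naturalness removed (human = 0%, levels 5 to 1 = 19 to 95%, or the final percentages if adjusted), beside the omnibus Level test.
- Apply it first to the deviant difference-wave MMN in the autistic group, since the MMN selects the Stage 3 voice. Treat other components, standard stimuli and the control group as supporting, so that the number of lead tests stays at one.
- Fit it in a model that accepts children who heard only three of the six blocks, such as a mixed model with child as a random effect. No child supplies all levels, so a complete-case repeated measures ANOVA over Level could not carry the contrast.
- Keep the omnibus, Tukey and Dunnett tests for threshold or non-monotone patterns and for choosing the voice.

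The cost is one additional planned test and no new data. Its downside is little power against non-monotone patterns, which the retained omnibus test covers.
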